## Definition for Evaluation of Secondary/Safety Study Objectives

## Safety Parameters

The safety objectives of the study will be evaluated from the following parameters (Safety Parameters):

- Incidence of AEs.
- Haematology, biochemistry, vital signs

## Description of Subject Groups for Analysis

## Definition of Subject Completion

A subject is considered to have completed the study if they have completed all study visits, including all cervico-vaginal sampling procedures and the follow-up visit.

## Definition of Datasets for Analysis

## Safety Dataset

The Safety Dataset includes all subjects who were randomised in to the study and received at least one application of study medication, whether they dropped out during the study or not.

## Per Protocol Dataset

The Per Protocol Dataset includes all subjects who are randomised in to the study, and completed at least two treatment periods including the 0 h sampling time point and do not have any major protocol violations.

## Datasets analysed for determination of study endpoints and analysis

## Primary Endpoints

The primary endpoints will be determined from the Per Protocol dataset.

## Safety Analysis

The Safety analysis will be conducted using the Safety dataset.

## Sample Size Estimation

Twelve participants have been chosen for an initial evaluation of the retention of SPL7013 amount and antiviral activity over time after application of SPL7013 Gel. No formal statistical determination has been performed as these parameters have not been previously assessed and therefore no information exists about the variability of these endpoints. The number of study participants has been chosen as a reasonable number for an initial assessment of the primary endpoints.

## Statistical and Analytical Plan

For the primary endpoints of prevention of HIV and HSV ex vivo, the antiviral activity will be measured as a percent inhibition of replication of each virus (% inhibition) . The level of inhibition from samples taken immediately after product application (time=0) will be the Baseline reference value (100% inhibition) for each subject. The level of inhibition at all other time points will be expressed as % inhibition relative to the level of inhibition at Baseline. The comparison of mean % inhibition will be performed for each time point versus that at Baseline using an appropriate statistical test to determine if there is a statistically significant decrease in activity compared to 0 hours. If there is a statistically significant difference between the values at each time point and the 0 hour time point, comparisons may be made between the other time points.

The mass and concentration of SPL7013 in CV samples at each time point (mass is calculated from the measured concentration of SPL7013 in each CV sample) will be compared to the values immediately after application using an appropriate statistical test as outlined below. If possible (i.e. the semi-log plot of mass or concentration vs time is linear), an estimate of the half-life of SPL7013 mass and/or concentration in CV contents will be calculated.

Should the data be reasonably symmetrical and uncontaminated by outliers, a standard test such as the paired t-test will be used; if this test is compromised by outliers or an extremely non-normal distribution, then a rank-based alternative will be used. While this study has not been powered for this comparison, in the absence of any information regarding the variability of this response, this will enable an estimate to be made of the variability, so that future studies may be based on a reasonable assessment of power.

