| **Study Procedures:** | After a 4-week screening period, each subject will receive 5 single doses of 3% SPL7013 Gel with at least 5 days washout between doses. CV samples will be taken using an INSTEAD® SoftCup at screening and at 0, 1, 3, 12 and 24 hours after dosing in a randomised sequence. Three additional blank samples will be taken at pre-dose and a further sample at the follow-up visit. |
| **Lab Analyses:** | The following assays will be conducted on the CV samples:   - Cell culture-based assays to determine the levels of the anti-HIV and anti-herpes simplex virus (HSV) activity of SPL7013 in CV samples - Bioanalytical assay for concentration of SPL7013 |
| **Safety Parameters:** | Routine biochemistry, haematology and urinalysis, physical examination/medical history, adverse events. |
| **Statistical Analyses:** | 12 subjects have been chosen for this initial evaluation of the bioavailability and antiviral activity of SPL7013 in CV samples over time after vaginal application of 3% SPL7013 Gel. No formal statistical determination has been performed.  For the primary endpoints of prevention of HIV and HSV ex vivo, the antiviral activity will be measured as a percent inhibition of replication of each virus (% inhibition).The level of inhibition from samples taken immediately after product application (time=0) will be the Baseline reference value (100% inhibition) for each subject. The level of inhibition at all other time points will be expressed as % inhibition relative to the level of inhibition at Baseline. The comparison of mean % inhibition will be performed for each time point versus that at Baseline using an appropriate statistical test to determine if there is a statistically significant decrease in activity compared to 0 hours. If there is a statistically significant difference between the values at each time point and the 0 hour time point, comparisons may be made between the other time points.  The concentration and mass of SPL7013 in CV samples at each time point (mass is calculated from the measured concentration of SPL7013 in each CV sample) will be compared to the values immediately after application using an appropriate statistical test as outlined below. If possible (i.e. the semi-log plot of concentration and/or mass vs time is linear), an estimate of the half-life of SPL7013 concentration and/or mass in CV contents will be calculated. |

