## Number of Subjects

A total of 12 eligible subjects are to be enrolled into the study.

Drop-outs (as defined in Section 9) can be replaced at the discretion of the Sponsor.

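### Scaling HIV and HSV inhibition to each woman's single 0 h sample makes the analysed 0 h SD zero, carries 0 h noise into every later value, and can bias mean retention, usually upward

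*Protocol*

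**What the plan says.** All references are to the protocol.

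- **Scale.** Section 10.4 measures antiviral activity as percent inhibition of replication of each virus, then fixes the reference: "The level of inhibition from samples taken immediately after product application (time=0) will be the Baseline reference value (100% inhibition) for each subject". The synopsis carries the same plan: "The level of inhibition at all other time points will be expressed as % inhibition relative to the level of inhibition at Baseline".
- **Test.** Mean percent inhibition at each later time is compared with 0 h "to determine if there is a statistically significant decrease in activity compared to 0 hours". If the data are reasonably symmetrical, "a standard test such as the paired t-test will be used"; otherwise a rank-based test is used.
- **Purpose.** Section 10.4 accepts that the comparison is unpowered but adds that "this will enable an estimate to be made of the variability, so that future studies may be based on a reasonable assessment of power". Section 10.3 explains the lack of a sample size calculation: "no information exists about the variability of these endpoints".
- **Mass and concentration.** In the same section these are compared with their values immediately after application. No resetting to 100% is stated for them.
- **Data available.** Section 5.2: "A total of 12 eligible subjects are to be enrolled into the study". Section 7.2.1 allows one sample per application, so each woman has one 0 h sample, and it comes from a different application than each later sample.

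**The concern.** The choice of test is left open, but the scale is not. Once every woman's 0 h value is 100, the analysed 0 h column has no spread, and each later value is a ratio whose denominator is one noisy sample. A mean of such ratios is not in general the ratio of the means.

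Two things are at stake. First, the study is meant to provide the first variability figures for these endpoints, and on the planned scale it gives no SD at 0 h and no SD of percent inhibition at any single time. Second, upward bias makes a loss of activity harder to detect. Section 2.2 says the results will inform advice on how long before intercourse the gel may be applied, so a missed loss is the unfavourable error.

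Noise at 0 h is plausible. The samples come from separate applications over about 8 weeks and two menstrual cycles (Section 4). Section 2.3 accepts that the cup may miss an unknown part of the gel and that mixing in the vagina may be incomplete.

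**Working it through.** **Inputs.** n = 12 (Section 5.2). One 0 h sample per woman (Section 7.2.1). No SD, CV, correlation or significance level is given, so these are assumptions: CV from 3% to 30%, equal at both times; within-woman correlation ρ of 0 and 0.3; lognormal inhibition; two-sided 5%. The sample size has no calculation behind it, so there is no plan figure to reproduce.

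**Step 1: what the test becomes.** Let I_0 and I_t be measured inhibition and R_t = 100 × I_t / I_0. Then R_0 = 100 for every woman, with SD 0. The paired t statistic is mean(R_t − 100) / (SD(R_t)/√12), which is a one-sample test of a ratio against 100. Running both tests on one simulated data set gave identical t and p.

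**Step 2: bias of the mean ratio.** To second order, E(R_t) ≈ 100 × (μ_t/μ_0) × (1 + CV0² − ρ × CV0 × CVt). With no true loss and equal CVs this is 100 × (1 + CV²(1 − ρ)):

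| CV | ρ = 0 | ρ = 0.3 |
|---|---|---|
| 3% | 100 × (1 + 0.0009) = 100.09 | 100 × (1 + 0.00063) = 100.06 |
| 10% | 101.0 | 100.7 |
| 20% | 104.0 | 102.8 |
| 30% | 109.0 | 106.3 |

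Simulation of 200,000 trials agrees; the largest gap is 106.1 in the last cell.

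The sign is not fixed. The bias is upward only if CV0 > ρ × CVt. With CV0 = 10%, CVt = 50% and ρ = 0.5 the factor is 1 + 0.010 − 0.025 = 0.985, which is downward.

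**Step 3: bounded inhibition.** Percent inhibition cannot exceed 100, which a lognormal model ignores. With a beta model, ρ = 0 and no loss, the mean ratio is 100.01 for a 0 h mean of 98% (SD 1 point), 100.3 for 90% (SD 5), 101.8 for 80% (SD 10) and 106.2 for 70% (SD 15).

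**Step 4: SD of the contrast.** The SD of the raw within-woman difference is 100 × CV × √(2(1 − ρ)). At ρ = 0.3, no loss:

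| CV | SD of raw difference | SD of ratio |
|---|---|---|
| 10% | 11.8 | 11.9 |
| 20% | 23.7 | 24.3 |
| 30% | 35.5 | 37.7 |

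Rescaling therefore inflates the SD of the contrast by about 1%, 3% and 6%. It is not the SD of one sample (10, 20 or 30 points here), and the rescaled data cannot give that figure.

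**Step 5: error and power, n = 12.** With no loss and ρ = 0, the chance of declaring a decrease (nominal 0.025) is about 0.023 at CV 3%, 0.02 at CV 10%, 0.017 at CV 20% and 0.015 at CV 30%. The raw difference and the log ratio stay at about 0.025. Power to detect a true 15% loss:

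| CV | ρ | Ratio to 0 h | Raw difference |
|---|---|---|---|
| 3% | 0 or 0.3 | 100% | 100% |
| 20% | 0 | 36% | 44% |
| 20% | 0.3 | 51% | 58% |
| 30% | 0 | 16% | 23% |
| 30% | 0.3 | 23% | 30% |

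**Step 6: correlation between later contrasts.** With independent samples, two ratios sharing one 0 h value correlate at about 0.48 to 0.50, and two differences sharing it at 0.50. Changing the scale does not remove this.

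**The case against.** Much of the opposing case stands.

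- A reader might infer that fixing 0 h at 100% takes 0 h variability out of the analysis. It does not. The variability moves into every later ratio, and the one-sample test includes it.
- A reader might infer that the variability estimate is simply wrong. It is not. The ratio SD is a proper SD for a later study with the same relative endpoint, and the fair benchmark for a within-woman test is the SD of the paired difference, which differs little (Step 4).
- A reader might take the correlation between later contrasts as an effect of rescaling. It comes from sharing one 0 h sample and persists under the alternative.
- Size and direction rest on CVs the protocol does not give. If 0 h inhibition is near its ceiling, the bias is negligible. It can also reverse.
- Section 2.3 describes the aim as finding a gross drop. A few points of power for a 15% loss matter little to that, and a rank-based test is allowed.
- Raw inhibition is measured, so a 0 h SD could still be computed. Which summaries to tabulate is commonly left to the SAP, which is not shown.

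What does not stand is reading the comparison of means as one of raw values. The sentences just before it define 0 h as 100% and the other times relative to it, and the synopsis repeats this. The scale is set in the protocol and fits poorly with the section's own aim of supplying variability.

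**Conclusion.** The point holds in limited form. Certain from the text alone: the analysed 0 h SD is zero by construction, the paired test is a one-sample test of a ratio, and no 0 h or single-time SD on the measured scale is planned. Conditional on assumed CVs: an upward bias of about 0.1 point or less at CV 3%, about 1 point at CV 10%, 3-4 points at CV 20% and 6-9 points at CV 30%, with a power loss of about 7-8 points for a 15% loss at CV 20-30%. These figures assume equal CVs, ρ between 0 and 0.3, lognormal data and 12 women. The documents cannot say which row applies. This does not threaten the study's ability to show a gross drop, but it is worth correcting because the correction is cheap.

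**What to change.** In Section 10.4 and the synopsis:

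1. Analyse HIV and HSV inhibition as measured at all five times. Test the within-woman difference from the measured 0 h value, in line with what is planned for mass and concentration. A log ratio is an alternative where all values are positive; name one of the two in advance.
2. Report the SD at every time including 0 h, and the SD of the within-woman differences with its 95% CI. With 12 women that interval runs from 0.71 to 1.70 times the estimate, which a planner of the next study needs to see.
3. Keep percent of 0 h as a descriptive display only.

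Cost: a few sentences in two places, with no new samples, assays or visits. If 0 h inhibition is near 100%, almost nothing changes; if it is not, the error rate is restored and some power regained. The downside is that the headline result is no longer stated directly as percent retained, although a back-transformed mean log ratio would give a geometric-mean version of it.

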# PROTOCOL SYNOPSIS

| **Study Title:** | Assessment of local retention and duration of activity of SPL7013 following vaginal application of 3% SPL7013 Gel (VivaGel®) in healthy volunteers |
| --- | --- |
| **Short Title:** | Retention and duration of activity of SPL7013 after vaginal dosing |
| **Sponsor:** | Starpharma Pty Ltd |
| **Protocol Number:** | SPL7013-003 |
| **Development Phase:** | Phase 1 |
| **Proposed Indication:** | Prevention of HIV and HSV infection in women |
| **Primary Objective:** | The primary objective of the study is to assess the local retention and antiviral activity of SPL7013 in cervico-vaginal (CV) samples as a function of time after application of 3% SPL7013 Gel in healthy volunteers. |
| **Secondary Objective(s):** | The secondary objective of the study is to assess safety, including local tolerability and systemic safety. |
| **Hypothesis:** | The hypothesis is that SPL7013 remains bioavailable and antiviral activity is retained for a period of time after application. |
| **Primary Endpoints:** | Ex vivo activity in the inhibition of virus replication as measured in *ex vivo* replication assays for HIV and HSV using CV samples, and mass and concentration of SPL7013 determined from the CV contents taken at screening, 0[[1]](#footnote-2), 1, 3, 12 and 24 hours after vaginal application of 3% SPL7013 Gel and a further sample at follow-up visit. |
| **Secondary Endpoints:** | None. |
| **Safety Endpoints:** | Local and systemic toxicity |
| **Study Design:** | Single-centre, open-label, randomised, cross-over, Phase 1 study. Each subject will receive 5 single doses of 3% SPL7013 Gel with at least 5 days washout between doses. One CV sample will be taken after each dose application at screening and at 0, 1, 3, 12 and 24 hours after dosing in a randomised sequence. Three additional CV samples will be taken pre-dose for use in validation and as standards in the activity and content assays and a further sample at the follow-up visit. |
| **Sample Size:** | 12 healthy women |

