## Limitations of Study Design

It is acknowledged that CV fluid in itself has intrinsic antiviral properties, and that the amount, constituency and corresponding antiviral properties of the CV fluid will vary with the menstrual cycle. The volume and visco-elasticity of CV fluid tend to increase during the follicular development and decrease in the immediate postovulatory phase of the menstrual cycle [21].

The variation in antiviral properties is considered to be minimal in comparison with those of the active product, and therefore it is not expected to confound study results. Sampling at certain points within the menstrual cycle would lead to significant complexity within the study, and as variability is considered minimal, has not been considered necessary to build in to this study design. A baseline sample will provide an indication of the intrinsic antiviral activity of CV fluid in each woman.

The variation in volume throughout the menstrual cycle may lead to variation in the dilution of the SPL7013 samples taken throughout the study. The literature indicates a mean increase in daily CV fluid volume (SD) from 0.1 (0.01)mL on day -6 to 0.7 (0.40)mL on day -1 followed by a decrease to 0.6 (0.40)mL on day 0 [22], providing a mean variation of approximately 0.69mL. In the context of administration of a 3.5g application of SPL7013 Gel, this variation translates to an increase in percentage CV fluid in the CV fluid / SPL7013 Gel mixture in the vagina, from approximately 3% to 17%. This degree of variation is not considered significant within the context of the objective of the study which is to understand when a gross drop in SPL7013 and antiviral activity may occur, in order to provide an indication of dosing timings for future efficacy studies. At worst, the results will provide an under-estimate of activity and amount of SPL7013 remaining.

Magnetic resonance imaging techniques have demonstrated that coating of the vagina and cervix with microbicide gels reduces with time over the 24 hour period, with varying distribution [23]. It is also accepted that due to the anatomy of the vaginal vault and sampling method employed, an unknown proportion of the gel might not be accessed by the INSTEAD SoftCup. Both these factors may lead to an under-estimate of the activity and amount of SPL7013 remaining.

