# STATISTICS

## Criteria for Evaluation of Study Objectives

## Primary Endpoints

The endpoints for evaluation of primary study objectives (Primary Endpoints) are as follows:

- The total amount (mass) of SPL7013 in CV contents sampled at 0, 1, 3, 12 and 24 hours after application.
- The concentration of SPL7013 in CV contents sampled at 0, 1, 3, 12 and 24 hours after application.
- The ex vivo activity in the prevention of replication of HIV of CV contents sampled at screening and at 0, 1, 3, 12 and 24 hours after application.
- The ex vivo activity in the prevention of replication of HSV of CV contents sampled at screening and at 0, 1, 3, 12 and 24 hours after application.

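### Section 10.4 scales antiviral activity to each woman's 0 h sample and requires no drug-free comparison, so intrinsic cervico-vaginal activity can be read as retained SPL7013 activity

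*Protocol*

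**What the plan says.** Section 10.4 (repeated in the synopsis) fixes the measure, the reference and the comparison for the HIV and HSV activity endpoints.

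- Measure: "the antiviral activity will be measured as a percent inhibition of replication of each virus". The control that corresponds to 0% inhibition is not named.
- Reference: the 0 h post-dose sample "will be the Baseline reference value (100% inhibition) for each subject".
- Scale: "The level of inhibition at all other time points will be expressed as % inhibition relative to the level of inhibition at Baseline".
- Test: "The comparison of mean % inhibition will be performed for each time point versus that at Baseline using an appropriate statistical test". If the time points differ significantly from 0 h, "comparisons may be made between the other time points".

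Elsewhere the protocol gives drug-free samples a role. Section 2.3 acknowledges that CV fluid is itself antiviral and adds: "A baseline sample will provide an indication of the intrinsic antiviral activity of CV fluid in each woman". Section 10.1.1 defines the HIV endpoint as activity against "replication of HIV of CV contents sampled at screening and at 0, 1, 3, 12 and 24 hours after application", with matching wording for HSV. The synopsis goes further and lists sampling "after vaginal application of 3% SPL7013 Gel and a further sample at follow-up visit" among the primary endpoints; Section 10.1.1 omits follow-up. Section 7.2.1 assigns the three pre-dose samples to assay validation and to use as assay standards.

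**The concern.** The primary objective is how long SPL7013 and its antiviral activity persist, and Section 2.2 intends the answer to support advice on how long before intercourse the gel may be applied. To say that activity has ended, one must know what a sample without drug looks like. The required analysis shows only how far a sample has fallen from the 0 h peak. If CV fluid alone inhibits replication, a late sample can show appreciable relative inhibition with no drug effect behind it.

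The terminology adds to the problem. In Sections 2.3 and 7.2.1 a baseline sample is drug-free; in Section 10.4 Baseline is the sample taken minutes after dosing. The drug-free sample that Section 2.3 relies on therefore has no stated place in the required analysis.

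**Working it through.** The protocol gives no numerical value for intrinsic or 0 h inhibition, and Section 10.3 says the sample size of 12 was chosen without calculation. There is no stated figure to reproduce. The check asks what the planned ratio returns for known amounts of drug effect.

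**Inputs (all assumptions)**
- b = inhibition by drug-free CV fluid: 0, 10, 30 or 50%.
- I_0 = inhibition at 0 h: 99%, with 90% as an alternative.
- d = inhibition due to the drug itself at time t: 0, 25 or 50%.
- Combination rule: I_t = 1 − (1 − b)(1 − d) (Bliss independence).
- 0% inhibition is read against a control without CV fluid.

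**Formulas**
- Planned ratio: R = I_t / I_0.
- Background-corrected ratio: C = (I_t − b) / (I_0 − b).

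**Step 1: no drug effect left (d = 0).** Then I_t = b, so R = b / I_0 and C = 0. This step does not depend on the combination rule.

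| b | R at I_0 = 99% | R at I_0 = 90% | C |
|---|---|---|---|
| 0% | 0% | 0% | 0% |
| 10% | 10/99 = 10.1% | 10/90 = 11.1% | 0% |
| 30% | 30/99 = 30.3% | 30/90 = 33.3% | 0% |
| 50% | 50/99 = 50.5% | 50/90 = 55.6% | 0% |

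**Step 2: some drug effect left (I_0 = 99%, b = 30%).**
- d = 25%: I_t = 1 − 0.70 × 0.75 = 47.5%. R = 47.5/99 = 48.0%; C = 17.5/69 = 25.4%.
- d = 50%: I_t = 1 − 0.70 × 0.50 = 65.0%. R = 65.0/99 = 65.7%; C = 35.0/69 = 50.7%.

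The gap between R and C is 30.3, 22.6 and 15.0 percentage points for d = 0, 25 and 50%. It is largest when the drug effect is gone, which is where the duration question is decided.

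**Step 3: the alternative control.** If 0% inhibition is instead read against drug-free CV fluid, the background is already removed and the gap largely disappears. The protocol does not say which applies.

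**The case against.** A reader might infer that the drug-free samples are never used and that intrinsic activity is certain to be counted as drug activity. The protocol does not support either statement.

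- Screening is a sampling point of both activity endpoints, so it can be read as one of the other time points in Section 10.4 and compared with 0 h. The clause on further comparisons would then allow 24 h against screening. This stands, but screening against 0 h does not show whether a late sample exceeds the drug-free level. The comparison that would show it is optional and depends on prior significance against 0 h.
- The pre-dose samples serve as standards in the activity assays, so the 0% point may already be drug-free CV fluid. This also stands as a possibility, and it is why the point is conditional.
- SPL7013 mass and concentration are primary endpoints measured in the same samples. A late sample without drug would show as such. This limits the harm but does not correct the activity endpoints.
- Section 2.2 disclaims separating active, vehicle and CV fluid, and Section 2.3 seeks only a gross drop. A fall from 100% to somewhere between 10% and 51% would still be visible. However, a comparison with the same woman's drug-free sample needs no separation of components and no placebo arm.
- Section 2.3 calls variation in intrinsic activity minimal relative to the product. The floor comes from the level of intrinsic activity and would exist with no variation at all.
- Section 2.3 also names sources of under-estimation: dilution, and gel that the cup does not reach. The net direction of error in the study is therefore unknown; only this component runs upward.

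A reader might also argue that averaging ratios over a noisy 0 h denominator inflates the mean materially. The protocol gives no variability on which to base this. With a mean of 99% on a 0–100% scale, the standard deviation cannot exceed √(0.99 × 0.01), about 10 points. That argument is not relied on here.

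**Conclusion.** The point holds in conditional form. The protocol fixes a ratio to 0 h as the activity measure and requires no comparison with drug-free samples, although it recognises intrinsic activity and makes screening activity part of two primary endpoints. Unless the unstated 0% control is drug-free CV fluid, a sample with no drug effect would be reported at b/I_0: about 10, 30 or 51% for b of 10, 30 or 50% and I_0 of 99%, and zero if b is zero. These inputs are assumptions; the documents do not give the actual level.

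Only the HIV and HSV activity endpoints are affected. The study is small, exploratory and has direct drug measurement alongside, so this should be fixed before analysis but does not undermine the study as a whole.

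**What to change.** In Section 10.4 and the matching synopsis text:

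1. State the control that defines 0% inhibition in each assay.
2. Report absolute % inhibition at every sampling point, beside any relative value.
3. Pre-specify a within-woman comparison of each post-dose time point with her drug-free level (screening and follow-up samples), beside the comparison with 0 h. Alternatively, use the background-corrected ratio (I_t − I_free)/(I_0 − I_free).
4. Use different terms for the drug-free baseline and the 0 h reference.
5. Make the synopsis and Section 10.1.1 agree on whether the follow-up sample belongs to the primary endpoints.

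The screening and follow-up samples are already in the schedule, so no visit, sample or arm is added. The cost is revised wording and slightly more analysis, and reported retained activity may look lower. Treating the follow-up sample as drug-free assumes complete washout; its SPL7013 concentration can confirm this.
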